## Abstract

**Background:**

Despite the availability of highly effective HIV pre-exposure prophylaxis (PrEP), uptake and adherence to PrEP among young men who have sex with men (YMSM) remains low, limiting its impact on the prevention of HIV infection. Strategies that incorporate an array of prevention options and provide YMSM and their providers with tailored education and support tools, including tools to support shared decision-making, are needed.

**Objective:**

The goals of the Centers for Disease Control and Prevention (CDC)–funded PrEP Choice study include the development and deployment of CDC guideline–consistent PrEP provider training and the implementation of evidence-based provider- and client-facing PrEP education and support tools. Under this initiative, the CDC funded 2 research projects, Florida State University (the Expanding PrEP in Communities of Color [EPICC] project), and Columbia University (the mChoice project).

**Methods:**

Providers from both projects will complete the PrEP Choice online training, which was developed to educate providers on PrEP options and how to engage clients in open discussions around sexual health and PrEP options. EPICC project providers will also attend online tailored motivational interviewing (TMI) training sessions, and mChoice project providers will view a training video on cultural competency and humility in PrEP care. Following training, each project will enroll a cohort of 400 participants receiving care from study providers and follow them for 12-18 months. Participants will complete online surveys every 3 months and provide biomarkers to assess PrEP adherence. Electronic health record (EHR) data will be collected every 6 months to provide additional information on clinic attendance, PrEP prescriptions, and HIV/sexually transmitted infection (STI) testing. Each project will provide cohort participants with a unique digital health tool to support the PrEP choice and ongoing adherence. The study will assess the effectiveness of training and educational and support tools in practice and the critical factors associated with the successful uptake of and adherence to PrEP by participants. The study will also monitor patterns of PrEP use among YMSM, including types of PrEP and switching between types.

**Results:**

Formative work to develop and prepare the tools for implementation was completed in 2023. The EPICC project began provider training in early 2024, and the mChoice project began in spring 2024. Cohort enrollment for both projects began after provider training began.

**Conclusions:**

Given the changing PrEP landscape, implementation of provider education and tools to maximize uptake and adherence is needed. By delivering culturally competent and interactive provider training on PrEP options, the study will help providers counsel and guide participants on the effective and safe use of PrEP. The digital health tools created will support participant adherence to help them optimize PrEP benefits. Through the cohort design, the PrEP Choice study will provide real-world data about PrEP use that will be critical for informing future guidelines and tools.

**International Registered Report Identifier (IRRID):**

DERR1-10.2196/64186

## Introduction

### Background

Young gay, bisexual, and other young men who have sex with men (YMSM) are the population most affected by HIV in the United States. Among all HIV infections diagnosed in 2021, 67% were found in MSM [1]. Racial and ethnic disparities persist in HIV diagnoses among MSM, with 36% of diagnoses among Black or African American (Black) MSM and 33% among Hispanic or Latino (Hispanic) MSM, compared with 25% among White MSM, despite smaller overall populations of Black and Hispanic MSM compared with those of White MSM. HIV can be prevented with the use of HIV pre-exposure prophylaxis, or PrEP [2]. The US Food and Drug Administration has approved the use of 3 antiretroviral drugs for PrEP by MSM: oral emtricitabine and tenofovir disoproxil fumarate (F/TDF) in 2012, followed by the availability of generic F/TDF in 2021; oral emtricitabine and tenofovir alafenamide (F/TAF) in 2018; and long-acting injectable cabotegravir (CAB-LA) in 2021. Clinical trials of sexual event-driven PrEP regimens or 2-1-1 PrEP using F/TDF have demonstrated it to be highly effective for HIV prevention among MSM [3,4]. These options provide MSM with choices about their preferred PrEP regimen; however, little is known about the PrEP choices men make, their switching between PrEP options, and the reasons for these decisions.

PrEP coverage continues to increase markedly among men [5]. However, findings from analyses of limited race and ethnicity data for PrEP users suggest racial and ethnic disparities exist in coverage. These PrEP use disparities are especially concerning in the context of large racial and ethnic disparities in HIV diagnoses, because men who might most benefit from PrEP are not being prescribed it, and among those prescribed, adherence remains suboptimal [6-9]. To accomplish the goals of the “Ending the HIV Epidemic in the US” initiative to reduce new HIV diagnoses by 90% by 2030, increase PrEP coverage to 50% of individuals with indications, and achieve health equity [10], it is imperative to overcome racial and ethnic disparities in PrEP use.

The implementation of effective interventions is needed to increase PrEP initiation, adherence, and persistence among YMSM. YMSM need tailored education with autonomy-supportive communication related to the growing array of PrEP options, and providers who serve these clients also need education and clinical decision-making support. Implementation of resources that discuss all PrEP options and emphasize shared clinical decision-making have the potential to enhance PrEP outcomes among YMSM, including PrEP initiation, adherence, and persistence [11]. Increased understanding of PrEP use patterns, including switching among PrEP options, is needed to optimally support lifetime HIV prevention among YMSM. Using evidence-based PrEP care as a guide, provider and patient education and support tools have been developed to assist in the provision of PrEP care. Evidence-based provider and patient education and support tools (EBTs) are available but are not being routinely used in clinical settings to increase PrEP screening, counseling, initiation, adherence, and persistence by YMSM [2,12,13]. To date, there has been a lack of research on the impact that existing informational materials have on PrEP provision or how tailoring these materials to meet the needs of providers and YMSM from diverse backgrounds could enhance their effects. Further, although EBTs for both providers and YMSM are available, these resources do not acknowledge or incorporate information about a growing arsenal of prevention products nor do they maximize opportunities to engage in a shared decision-making process about these products [14,15].

Provider education can support clinicians to provide recommended PrEP services and to maintain up-to-date knowledge of PrEP options. Patient education using adapted EBTs can help men understand how PrEP can support their sexual health and learn about the PrEP options available to them. Adherence and persistence support tools, such as user-friendly apps, can support men prescribed PrEP to take their medication as directed and to continue to use it for as long as they can benefit from its protection. Increased understanding of PrEP use patterns, including switching among PrEP options, is needed to optimally support YMSM to use PrEP that is appropriate for them at various times in their lives.

### Aims and Objectives

The goals of the Center for Disease Control and Prevention (CDC)–funded study, known as the PrEP Choice study, include the development and deployment of CDC guideline–consistent PrEP provider training and the implementation of evidence-based provider- and participant-facing PrEP education and support tools [13,16]. PrEP support tools include innovative, customized mobile apps. The study will also conduct a longitudinal assessment of YMSM who are initiating or persisting with PrEP to understand their preferences for PrEP modalities and changes in PrEP use over the course of the study. The study will assess the implementation context, assess the effectiveness of provider training and EBTs in practice, and analyze the critical factors associated with successful uptake of and adherence to PrEP by participants enrolled in the study.

Under this initiative, the CDC funded 2 research projects, at Florida State University (the Expanding PrEP in Communities of Color [EPICC] project) and at Columbia University (the mChoice project). The PrEP Choice study is a 5-year initiative; funding began on September 30, 2021. In this paper, we discussed both EPICC and mChoice Studies, as they are supported under the same funding announcement, use the same PrEP training modules, use similar instruments for their longitudinal cohorts, share the same eligibility criteria, and incorporate digital health tools.

Through these 2 studies, we will test the effectiveness of provider training to increase provider knowledge of and comfort with PrEP modalities in clinical practice; evaluate the feasibility and acceptability of implementing provider training; describe the barriers and facilitators impacting the implementation of new PrEP modalities in clinical practice; test the effectiveness of provider training and digital tools to increase PrEP adherence and persistence among YMSM; and describe real-world PrEP use, including factors influencing the selection and change of PrEP regimens.

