### Study Design

The EPICC project includes 2 distinct aims. Aim 1 includes provider training. Providers will be trained on the use of education tools adapted in the formative work and the process of screening, counseling, initiation, and follow-up with clients interested in or already taking PrEP through our PrEP training modules and will complete TMI training. The effectiveness of the training will be measured quantitatively. Aim 2 is a longitudinal cohort study designed to test the newly adapted education tools through a hybrid type 2 effectiveness implementation cohort to assess PrEP uptake and adherence to PrEP among YMSM and provider provision of PrEP and competence with education tools to increase PrEP services. Aim 2 will include a mixed methods analysis. Figure 1 provides an overview of the EPICC project’s design. Formative work can be found elsewhere [17].

The mChoice project includes 3 aims. Aim 1 of the mChoice project is to conduct a hybrid type 2 trial testing the effectiveness of the mChoice clinical intervention to increase PrEP adherence and persistence among YMSM using PrEP. Aim 2 is to conduct in-depth interviews to assess multilevel factors at the patient level associated with selection of a PrEP regimen and switching patterns. Aim 3 is to provide training to health care providers to improve knowledge of PrEP clinical recommendations and enhance provider communication. Figure 2 provides an overview of the mChoice project design. Formative work findings can be found elsewhere [18].

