### Data Collection

Every 6 months, study sites (EPICC and mChoice) will complete a clinic assessment that will include information around PrEP prescriptions issued, clinic services, financial assistance, and PrEP support services. This information will be collected prior to the provider training and will continue for the duration of the study to assess implementation efficacy. There will be a clinic assessment baseline and final, which is completed at the beginning of data collection and at the end and a shorter clinic assessment every 6 months. These assessments will capture data on clinic demographics, PrEP uptake and follow-up and provision of HIV and PrEP education.

The EPICC project’s aim 1 provider training consists of the completion of surveys prior to and after training components. Providers are rated on their use of TMI during standard patient interactions immediately after training and three months post training. Aim 2 data collection will occur using surveys every three months, project app paradata, and exit interviews. Additionally, we will conduct focus group discussions with providers at the end of the longitudinal cohort.

The mChoice project’s aim 1 data collection will occur using surveys every three months, and project app paradata. Aim 2 data collection will occur using in-depth interviews with a subsample from aim 1. The mChoice project’s aim 3 provider training consists of the completion of surveys prior to and after training components and an interview following completion of the training.

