## Results

The EPICC project formative work to develop evidence-based tools ([name] et al, unpublished data, March 2025) was completed in April 2023 [17]. Provider training enrollment began in January 2024 and was completed in August 2024. Cohort enrollment began in April 2024. As of October 2024, 40 participants were enrolled in the EPICC project cohort. Cohort enrollment is expected to be completed in September 2025, with the final results anticipated in early 2027. Provider focus groups are expected to begin in April 2026, with the final results expected in early 2027.

The mChoice project formative work to develop and evaluate evidence-based tools was completed in January 2024 ([name] et al, unpublished data, March 2025) [18,46]. Provider training enrollment began in June 2024 and is ongoing. Cohort enrollment began in July 2024. As of October 2024, 18 participants were enrolled in the mChoice project cohort. Cohort enrollment is expected to be completed in July 2025. The final results are expected in late 2027.

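### The cohort's baseline-to-follow-up contrast does not identify the effect of provider training, or of training plus app, and cannot show an effect on being prescribed PrEP

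*Protocol article*

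**What the plan says.** Aims and Objectives states that the two projects will "test the effectiveness of provider training and digital tools to increase PrEP adherence and persistence among YMSM". The same section says the study will "analyze the critical factors associated with successful uptake of and adherence to PrEP by participants enrolled in the study". Study Design describes EPICC's Aim 2 as a "hybrid type 2 effectiveness implementation cohort to assess PrEP uptake and adherence to PrEP among YMSM".

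On order, the abstract's Methods paragraph says: "Following training, each project will enroll a cohort of 400 participants receiving care from study providers". The abstract's Results paragraph says only that cohort enrolment opened after training had begun. The Results section gives project-level dates:

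- EPICC enrolled providers for training from January to August 2024 and opened its cohort in April 2024.
- For mChoice: "Provider training enrollment began in June 2024 and is ongoing. Cohort enrollment began in July 2024".

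The payment schedules under Ethical Considerations tie the app download to the baseline survey in both projects. Eligibility, under Longitudinal Cohort, requires every participant to hold a current PrEP prescription, whether new or a refill.

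The EPICC power section includes a baseline-to-postintervention contrast. The mChoice primary analysis compares outcomes before and after the intervention. Data Collection also describes clinic assessments that cover prescriptions issued and PrEP uptake: "This information will be collected prior to the provider training and will continue for the duration of the study to assess implementation efficacy".

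**The concern.** A before-after design without a control group rests on its before value. Here two intervention components start at different times: training is meant to come before enrolment, and the app starts at enrolment. The cohort baseline is a before value for the app only. It is not one for training, nor for the two together.

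The stated aim joins both components and attaches them to adherence and persistence. If adherence rises, the wording invites the conclusion that training plus app raised it, which the contrast cannot support. If adherence does not rise, a training benefit already reached by enrolment would be missed. The Limitations section concedes that the study is not randomised, but it does not mention that baseline follows training.

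Uptake raises a separate problem. A cohort made up entirely of people with a prescription has no one in whom becoming prescribed could be observed.

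**Working it through.** **Step 1: what the contrast estimates.** On an additive scale, let μ be the outcome level before training, β the full training effect, f the share of β already present at enrolment, A the app effect and T any change over time.

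- Baseline = μ + fβ
- Follow-up = μ + β + A + T
- Difference = (1 − f)β + A + T
- Package effect named in the aim = β + A

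This gives one observed difference and four unknowns. With T = 0, a 9-point difference fits each of these:

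- β = 0, A = 9
- β = 9, f = 0, A = 0
- β = 18, f = 0.5, A = 0, since (1 − 0.5) × 18 = 9

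Nothing in the cohort design chooses among them.

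**Step 2: the plan's own figures (EPICC, Sample Size and Power Calculations).** Inputs: 400 participants, 15% loss, reference rate 20%, one-sided 0.05, power 0.80. Evaluable n = 400 × 0.85 = 340.

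- *5.6 points.* A one-sample test against a fixed 20% solves Δ√340 = 1.645√(0.20 × 0.80) + 0.842√(p₁(1 − p₁)), with p₁ = 0.20 + Δ. This gives Δ = 5.56 points, so the figure reproduces. The comparison it matches is with a fixed rate, not with an untrained group. Two independent groups of 170 would give 11.8 points.
- *About 9 points (odds ratio 1.6).* Going from 20% to 29% is (0.29/0.71)/(0.20/0.80) = 1.63. A closed-form paired contrast with n = 340 gives a minimum of 8.1 points at within-person correlation 0 and 6.7 at 0.3. The simulated 9 is therefore of the right order and somewhat conservative.

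For mChoice the baseline rate is not given, so its sample size of 400 cannot be checked exactly.

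**Step 3: what a late baseline could hide.** This is an illustration; the documents do not give the share. Suppose that the package moves the rate from 20% before training to 29%, that T = 0, and that a share g of those 9 points is present at enrolment. Then:

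- p_a = 0.20 + 0.09g and d = 0.29 − p_a
- v = p_a(1 − p_a) + 0.29 × 0.71 − 2ρ√(p_a(1 − p_a) × 0.29 × 0.71)
- power = Φ(d√(340/v) − 1.645)

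| g | visible contrast (points) | power, ρ = 0 | power, ρ = 0.3 |
|---|---|---|---|
| 0 | 9.0 | 86% | 95% |
| 0.25 | 6.75 | 65% | 78% |
| 0.5 | 4.5 | 38% | 48% |
| 0.75 | 2.25 | 16% | 19% |
| 1 | 0 | 5% | 5% |

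**Step 4: how much of the cohort has a post-training baseline.** By October 2024 EPICC had 40 of 400 enrolled, and provider enrolment for training had closed in August. At least 360/400 = 90% of the planned cohort therefore enters after that closure. In mChoice, 382/400 = 95.5% enters after October 2024, at least four months after training opened, but training enrolment was still running, so no equivalent bound exists.

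**Step 5: uptake.** Holding a prescription is an entry condition, so its proportion at baseline is 100% by design. There is no non-user denominator in which training or the app could change it.

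**The case against.** The strongest reply is that the aim concerns a package, that training has its own provider-level outcomes with before-after tests, and that non-randomisation is already conceded. The provider-level tests are unaffected by this point. The package argument does not rescue the cohort contrast, because the cohort baseline is not a pre-package value either.

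A reader might infer several stronger things that the documents do not support:

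- *That the estimable training effect is exactly zero.* A provider's training date is not the date on which a patient first meets trained care. Refill patients can be recruited through advertisements before their next visit, and counselling continues over 12 to 18 months. Some training effect may therefore fall after baseline.
- *That some baselines are shown to precede training.* The Results section gives project-level dates of training enrolment, not completion dates by provider or site. Sites trained one after another, each before its own patients enrol, would fit both the dates and the abstract. In EPICC at most 40 of 400 participants could have enrolled while training enrolment was open.
- *That uptake is a formal cohort endpoint.* It is not a primary, secondary or powered cohort outcome. The text speaks of assessing it and of factors associated with it, and first dosing after a new prescription can still be described.
- *That the clinic data are unused.* They are collected to assess implementation, and the EPICC Analysis Plan models number of prescriptions as the primary implementation outcome over all time points. What is missing is a stated before/after-training term there, and any such model for mChoice.

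**Conclusion.** The point holds in this form: the cohort's baseline-to-follow-up contrasts do not identify the effect of provider training, nor of training plus app. They estimate change after app introduction among patients of trained providers, mixed with continuing trained care and with time. The size of the problem depends on the share of the effect present at enrolment, which is unknown. Over the full range from none to all, EPICC's 9-point effect would show as anything from 9 points to 0, with power from 86% to 5% at zero correlation. These figures assume a true 20% to 29% change, 340 evaluable participants and no time trend. No stated sample-size figure is shown to be wrong; the issue is which effect those figures refer to.

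The cohort also cannot show an effect on being prescribed PrEP. This follows from the eligibility rule alone and needs no assumption.

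This is not detail that could be left to an analysis plan, because the stated aim conflicts with the stated enrolment order and eligibility.

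**What to change.** 1. Restate the cohort aim and its conclusions, in both projects, as change after app introduction under trained-provider care, not separable from continuing trained care or time. Remove uptake from what the EPICC cohort assesses for effectiveness, and tie it to the clinic-level data.
2. Use the clinic assessments taken before training and every 6 months (prescriptions issued, PrEP uptake) for a clinic-level before-after analysis of training in both projects. In EPICC, add an explicit before/after-training term with clinic effects to the prescriptions model. In mChoice, specify an equivalent model.
3. Reconcile the abstract's statement that cohorts are enrolled after training with the overlapping dates in Results. If provider completion dates are available, which the article does not say, run a sensitivity analysis that excludes participants enrolled before their provider completed training. A time-varying trained/untrained covariate would add little in EPICC, where it would be nearly constant.

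The cost is wording and analysis, with no new recruitment. The headline claim becomes narrower. The clinic-level analysis will have limited precision because it rests on few clinics, and, being uncontrolled, it remains open to time trends.

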## Methods

### Ethical Considerations

This works follows a protocol reviewed and accepted by the Institutional Review Boards of Florida State University (approval number 00003623) and Columbia University (approval number AAAT8812). Participants will provide informed consent prior to beginning any study activities. The consent form includes standard consent sections describing the purpose of the study, the procedures to be followed, and the risks and benefits of participation. The consent form went through multiple reviews by team members to ensure the language was sufficiently simple. A certificate of confidentiality was obtained from the CDC. All data and records will be stored on password-protected servers. No identifiable data will be published.

EPICC project providers will be compensated US $50 for completing the pretraining survey; US $50 for completing online PrEP training modules, tailored motivational interviewing (TMI) training sessions, the posttraining survey, and the first standard patient interaction; and US $50 for the 3-month posttraining standard patient interaction. Cohort participants will be compensated US $50 for the baseline survey and app download, US $50 for an optional onboarding visit, US $25 for the 3-month follow-up survey, US $50 for the 6-month follow-up survey, US $25 for the 9-month follow-up survey, US $50 for the 12-month follow-up survey, US $25 for the 15-month follow-up survey, and US $50 for the 18-month follow-up survey. For home-based dried blood spot (DBS) collection, cohort participants will be compensated US $50 for the baseline, 6-month, and 12-month collections and US $75 for the 18-month collection. A US $50 bonus will be provided to participants who complete the first 3 collections. Participants who complete the exit interviews will be compensated US $50. Providers who complete focus group discussions will be compensated US $75.

mChoice project providers who complete the pre- and postassessment will be compensated US $50. Providers who complete an in-depth interview will be compensated US $100. Cohort participants will be compensated US $40 for the baseline survey and app download, US $45 for the 3-month follow-up survey, US $55 for the 6-month follow-up survey, US $60 for the 9-month follow-up survey, US $70 for the 12-month follow-up survey, and US $80 for the 18-month follow up survey. Cohort participants who complete an in-depth interview will be compensated US $35. Providers who complete an in-depth interview will be compensated US $100.

